## Abstract

**Background:**

The number of older adults with dementia is expected to increase. Dementia is not only characterized by a decline in cognition, also other functions, for example, physical functioning change. A possible means to decrease the decline in these functions, or even improve them, could be increasing the amount of physical activity. A feasible way hereto may be activation of the mirror neuron system through action observation. This method has already been shown beneficial for the performance of actions in, for example, stroke patients. The primary aim of this study is to examine the effect of observing videos of walking people on physical activity and physical performance, in older adults with dementia. Secondary, effects on cognition and quality of life related factors will be examined.

**Methods/Design:**

A cluster randomized controlled trial is being performed, in which videos are shown to older adults with dementia (also additional eligibility criteria apply) in shared living rooms of residential care facilities. Due to the study design, living rooms instead of individual participants are randomly assigned to the experimental (videos of walking people) or control (videos of nature) condition, by means of drawing pieces of paper. The intervention has a duration of three months, and takes place on weekdays, during the day. There are four measurement occasions, in which physical activity, physical functioning, activities of daily living, cognition, the rest-activity rhythm, quality of life, and depression are assessed. Tests for participants are administered by a test administrator who is blind to the group the participant is in.

**Discussion:**

This study examines the effect of the observation of walking people on multiple daily life functions and quality of life related factors in older adults with dementia. A strength of this study is that the intervention does not require much time and attention from caregivers or researchers. A challenge of the study is therefore to get to know for how long residents watch the videos. However, the design implies a high feasibility of the study, as well as a high applicability of the intervention into daily care.

**Trial registration:**

NTR4708. Date of registration: 31 July 2014.

## Background

During the second half of the last century, there was a vast increase in the number of people aged 60 and above, from 205 million people worldwide in 1950 to 606 million people in 2000 [1]. This number is expected to increase to almost two billion in 2050. Within this group of older adults, the group of people aged 80 and above is increasing the fastest [2]. As age is an important risk factor for dementia [3], an increase is also expected in the number of people with dementia, from about 35.6 million people in 2010, to 115.4 million in 2050 [4]. One of the main characteristics of dementia is a progressive cognitive decline [5]. In the most prevalent subtypes of dementia, Alzheimer’s disease and vascular dementia [6], cognitive functions such as memory and executive functions (EF) already decline in an early stage of the disease, although in a different degree for both subtypes [7].

With the decline in cognitive functions, the dependency of people with dementia increases [5]. Indeed, for many subtypes of dementia, a decline in cognitive functions is associated with increasing limitations in activities of daily living (ADL) [8]. Other aspects of daily life functioning, such as physical functioning, are also altered in dementia. Functional mobility and muscle strength already decline over the adult lifespan [9], and physical functions such as mobility and lower extremity strength decline even more in people with dementia [10]. In both older adults and people with dementia also several gait disturbances are present [11]. Depending on the presence and subtype of dementia, these gait disturbances are, for example, wide base, decreased velocity, and decreased step length. Additionally, the rest-activity rhythm becomes weaker and more fragmented over the adult lifespan [12]. In people with dementia, many sleep disturbances such as a disrupted sleep-wake rhythm are present [13].

Because of the negative influences of dementia on multiple aspects of daily life, and no cure for dementia is available yet [14], it is of clinical relevance to find a way to decrease the decline in these functions or even improve them. This could be achieved by an increase in physical activity. Physical activity has been shown to have multiple beneficial effects for older adults in general. Not only is physical activity an important factor in maintaining health [15], it has also been found to be beneficial for mobility/physical functioning [16], to lower the risk of (progression of) ADL disability [17], to reduce depressive symptoms in older adults with depression [18,19], and, although based on only one study of 10 male participants, to influence the rest-activity rhythm by reducing its fragmentation [20]. Exercise may also have beneficial effects on several aspects of cognition, but the findings for this outcome measure are more equivocal [21,22]. The same holds for quality of life (QoL), on which beneficial effects have also been found in some but not all studies [23].

Despite the numerous beneficial effects of physical activity, many older adults are insufficiently active. Even though the percentage of older adults that meets the recommended physical activity level varies widely across studies, most of the reported percentages do not exceed 50% [24]. The level of inactivity is higher in older adults than in younger age groups [25], and people living in nursing homes or other residential care facilities seem to have even higher levels of inactivity than their community-dwelling counterparts [26-28]. Many people with dementia relocate to a nursing home, which implies they are at a higher risk of becoming sedentary. Being physically active is however not only found to be effective for older adults in general, also older adults with cognitive decline or dementia may experience beneficial effects from physical exercise. Beneficial effects have been reported on for example, mobility/physical functioning [29], ADL [10] and cognitive function [22]. However, for cognitive function findings were more equivocal [22].

Because of the beneficial effects of physical activity, it is important to motivate older people with dementia to become more physically active. Of all physical activities, walking is among the easiest to perform in daily life [30]. Many people are able to perform this activity, which makes walking a suitable activity to encourage older adults to do. However, it is time-consuming for caregivers to go for a walk with residents on a regular basis. Moreover, considering the expected increase in the number of older adults [1], as well as in the ratio of older adults to the working-age population [31], it will most likely become harder for caregivers to find time to motivate older people for and supervise them in the participation in a walking activity. A more feasible and less demanding way to increase walking and obtain its beneficial effects in older adults with dementia may be activation of the mirror neuron system (MNS) through action observation.

Mirror neurons become activated both when people perform an action themselves, and when they see someone else perform the same action [32]. The MNS seems to become activated only if an observed action exists in one’s own motor repertoire [33], and it becomes activated more if the specific motor skill observed is acquired better, that is, expertized [34]. Clearly, for ambulatory people, walking is an action that meets both these ‘requirements’. Walking can be considered a voluntary movement, as opposed to an affective movement. The MNS that is activated in the recognition of voluntary movements, the parietofrontal MNS, consists of the parietal lobe, the premotor cortex (PMC), and the posterior inferior frontal gyrus [33]. Both the PMC and the parietal lobe are activated in a somatotopic way [35]. Areas that are activated during observation of foot movements related to an object (e.g., ball kicking), are the dorsal sector of Brodmann’s area 6, and posterior parts of the parietal lobe (Brodmann’s areas 7 and 39). In addition, during observation of a person walking corticospinal excitability has been found to increase [36].

Observation of an action seems to have a facilitative effect on the execution of the observed action, as has been found for the movement onset of finger movements [37]. Furthermore, activation of the MNS through action observation has been shown beneficial, for example, for the rehabilitation of motor functions after stroke [38]. In the described studies, participants that both observed and executed a specific action (i.e., action observation therapy), showed a larger improvement in the function concerned than participants who performed the action without observing it. Action observation therapy has also been shown to decrease the number of freezing of gait episodes in patients with Parkinson’s disease for a longer period of time than practicing the action and watching images of landscapes [39]. Another pilot study showed a greater improvement in daily actions in patients with Parkinson’s disease who received action observation therapy, than in patients who performed the actions and watched videos in which no physical movements were shown [40].

Based on among others the activation of the PMC and the corticospinal excitability induced by observing an action, observing a certain movement (e.g., walking) may facilitate people to initiate the execution of that movement. This may increase their amount of physical activity. Furthermore, based on the effects of action observation therapy on the execution of the observed action, and the beneficial effect of physical activity on physical functioning and ADL, these physical performance measures may also improve. This would imply that also the quality of movements may improve as a result of action observation. Thus, the primary hypothesis in this study is that the observation of videos of walking people will have a beneficial effect on the amount of physical activity (walking) as well as on physical performance (the ‘quality’ of movements, e.g., physical functioning and ADL) in older adults with dementia. In addition, secondary effects may follow directly from action observation and/or indirectly through an increase in physical activity. The secondary hypothesis, therefore, is that the observation of videos of walking people has beneficial effects on cognition and QoL related outcomes (i.e., the rest-activity rhythm, QoL and depression). In sum, this study aims to examine the effects of observation of walking on physical, cognitive, and QoL related outcome measures in older adults with dementia.

## Methods/Design

### Study design

Reporting the design of this study follows the CONSORT guidelines [41] as strict as possible, except for the guidelines for the results and discussion sections, as this is a study protocol. This study is a cluster randomized controlled trial (RCT). The data is hierarchically ordered with participants (level 2) nested within living rooms (level 3) and four measurement occasions per participant (level 1). Since randomization at level 2 is not possible due to the study design, block randomization is being performed at level 3 where for each set of two living rooms of residential care facilities, the living rooms are randomly assigned to the experimental or control condition, thereby taking into account an evenly divided number of living rooms per condition. When a single additional or separate living room is included, and an even number of living rooms has been included before, this single living room is randomly assigned to the experimental or control condition. However, when an odd number of living rooms has been included before, the single living room is assigned to the condition that occurred least before. Randomization at level 3 is necessary since residents of the control condition should not be able to see the videos of the experimental condition, and vice versa. The complete randomization process is performed by the researcher, and randomization occurs by drawing pieces of paper. These pieces of paper are equally sized and folded, so that the drawing process occurs blindly.

### Setting

This study takes place in residential care settings, such as nursing homes. Due to the design of the study, these care settings need to have at least one living room in which residents with dementia are present during the day. The care settings are located in the Netherlands, and optionally in other European countries.

### Participants

The participants should be older adults (aged 70 years and older) with a diagnosis of dementia (as stated in their medical files). In addition, they should have a score of ≤25 on the Dutch version of the Mini-Mental State Examination (MMSE) [42]. This score is indicative of at least mild cognitive decline. This criterion was changed after trial commencement, from the preceding inclusion criterion of an MMSE score of 15–25. It was decided that residents with a lower score could also be included, as most outcome measures can be assessed for them as well. Only for cognitive functioning a shortened neuropsychological test battery is used for participants with an MMSE score <15 (see ‘Measurement occasions’ under the heading ‘Procedure’). For inclusion it is furthermore important that participants are usually present in the living room during the day.

Exclusion criteria are: a history of alcoholism, cerebral trauma, hydrocephalus, neoplasm, history of depression, personality disorders (other than those based on dementia), disturbances of consciousness, not being ambulant, and visual impairments. The last-mentioned exclusion criterion should be interpreted in such a way that participants should be able to see the videos, and to see visual stimuli during the test assessments. For the test assessments, it is also important that participants’ hearing is sufficient.

The following possible confounders are registered if available: subtype of dementia, age, gender, education level (using the Verhage system [43], with scores ranging from 1 = less than six grades of primary education to 7 = university), the use of visual, hearing, or walking aids (including the type), comorbidity, and medication use.

### Power calculation

A power analysis for a 2 x 4 mixed factorial design with two groups and four measurement occasions, with α = .05, β = .80, and an effect size of f(V) = .25, resulted in *n* = 179 participants. Taking into account a dropout of 10%, this results in a total of *n* = 199 participants. This power calculation was performed using G*Power 3.1.4 [44].

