**Overview of the study protocol.**

#### Inclusion of participants

The selection of residents is based on the criteria mentioned under the heading ‘Participants’, which are verified by means of the medical files of the residents, in consultation with the medical or nursing staff. The selected residents are asked whether they would like to participate, and their legal representative/contact person is contacted to ask for his/her permission as well. Subsequently, the MMSE is administered; if the score is ≤25, and if the person’s vision and hearing is sufficient based on observations during this test, written consent is asked from the legal representative/contact person and from the resident. When at least two residents in a living room agree to participate, the living room can be included in the study by the researcher.

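### The 179/199 sample size assumes independent participants although living rooms are randomised, so the stated 80% power does not hold if changes over time correlate within rooms

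*Protocol article*

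**What the plan says.** The Study design section of the protocol article calls the trial a cluster randomised trial and sets out three levels, with four occasions per participant at the lowest: "The data is hierarchically ordered with participants (level 2) nested within living rooms (level 3"). Randomisation takes place at living-room level because it cannot be done within a room. The Statistical analysis section follows this structure, with mixed models that have living room as level 3 and participant as level 2. The group-by-time interaction is the sign of a treatment effect.

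The Power calculation section describes something simpler: "A power analysis for a 2 x 4 mixed factorial design with two groups and four measurement occasions". Its error rates and assumed effect are given as "with α = .05, β = .80, and an effect size of f(V) = .25". By its own account the calculation "resulted in *n* = 179 participants". On dropout it then says: "Taking into account a dropout of 10%, this results in a total of *n* = 199 participants". The software is named: "This power calculation was performed using G*Power 3.1.4".

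On room size the article gives only a minimum, in Inclusion of participants: "When at least two residents in a living room agree to participate", the room may enter. It states no average room size, number of rooms, ICC or design effect.

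**The concern.** A mixed factorial design of two groups by four occasions has participants and occasions but no clusters. If the sample size was computed on that design, it counts 179 participants as 179 independent units, whereas the trial allocates whole rooms. Residents of one room share the same screens and the same switch-on and switch-off times. Caregivers complete the Katz ADL, a primary measure, and one caregiver may rate several residents of a room. Correlated changes within a room are therefore plausible, and any such correlation reduces the information in a given number of participants.

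The 80% is the only justification given for the size of the trial. A null result would be read as coming from an 80%-powered trial when the true power may be lower, and the Power calculation section gives the reader no means of judging by how much.

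**Working it through.** **Inputs from the Power calculation section.** α = .05; f(V) = .25, so f² = .0625; 2 groups; 4 occasions; N = 179; dropout 10%.

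**Step 1: reproduce the stated figure.** For the G*Power procedure for a repeated-measures MANOVA within-between interaction, the test is a noncentral F with

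- df1 = (2 − 1)(4 − 1) = 3
- df2 = N − 4
- noncentrality λ = N × .0625

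Results:

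- N = 178: power .7990
- N = 179: λ = 179 × .0625 = 11.19, power .8015

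So 179 is the first N to reach .80. Then 179 / .9 = 198.9, rounded up to 199. Both printed figures are reproduced exactly with a design effect of 1, so 179 contains no allowance for clustering.

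Other readings do not give 179. A univariate repeated-measures F with the same effect size gives 60 or 62. Repeated-measures ANOVA with f = .25 and an assumed correlation of .5 between occasions gives 24 (interaction) or 82 (between groups). Taking β = .80 literally, that is power .20, gives 38.

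**Step 2: add clustering.** The article supplies neither quantity needed, so both are assumptions: m participants per room, and the ICC of change over time (the relevant one for a group-by-time interaction). The design effect is DE = 1 + (m − 1) × ICC, and λ becomes N × .0625 / DE. For example, m = 5 and ICC .05 give DE = 1 + 4 × .05 = 1.20, λ = 11.19 / 1.20 = 9.32, and power 71.8%.

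The table gives power for 179 complete cases and for all 199 enrolled contributing fully. Because the mixed model can use the earlier occasions of participants who later drop out, the information from 199 enrolled lies between the two columns.

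| m | ICC | DE | Power, 179 | Power, 199 |
|---|---|---|---|---|
| – | 0 | 1.00 | 80.2% | 84.7% |
| 2 | .02 | 1.02 | 79.3% | 83.9% |
| 5 | .01 | 1.04 | 78.4% | 83.1% |
| 5 | .02 | 1.08 | 76.7% | 81.5% |
| 5 | .05 | 1.20 | 71.8% | 76.8% |
| 8 | .05 | 1.35 | 66.0% | 71.3% |
| 8 | .10 | 1.70 | 55.0% | 60.1% |

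**Step 3: other ways to express the loss.** At DE = 1.2, 80% power needs 214 analysed instead of 179. Equivalently, with 179 analysed the detectable f(V) rises from .25 to about .25 × √1.2 = .27.

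**Step 4: degrees of freedom.** The table keeps df2 = N − 4. Basing them on the number of rooms K (df2 = K − 4) lowers power further. With m = 6, ICC .05 and about 30 rooms (179 / 6), power is 63.5% instead of 69.8%.

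**The case against.** Several points on the other side are sound.

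- **Nothing is miscalculated.** 179 and 199 both follow from the stated inputs. The fault is that the sizing model does not match the design.
- **The planned analysis includes living room as level 3.** A reader might infer that clustered data will be analysed as if independent. The Statistical analysis section shows otherwise; only the planning statement is affected.
- **The size of the loss cannot be settled from the article.** Stable differences between rooms cancel in a group-by-time contrast, so the relevant ICC is that of change, which may be lower than that of a single measurement. A reader might take one of the lower figures above as the trial's actual power, but nothing in the article supports singling one out.
- **179 complete cases is the pessimistic bound.** If all 199 contribute fully, power stays above 80% at m = 5 and ICC .02 (81.5%). It does not at m = 5 and ICC .05 (76.8%).
- **β = .80 is a slip of notation.** Read literally it means 20% power, but that would need only 38 participants, so the authors plainly meant power of .80.

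A further defence is that a journal article condenses, and that an allowance for clustering may sit in the full protocol. That does not rescue the printed figure, because the exact match at design effect 1 leaves no room for a hidden allowance in 179.

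These points limit the claim about size. They do not remove the mismatch.

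**Conclusion.** The point stands as a mismatch between the sample size calculation and the design in the same article. The printed 80% belongs to a trial of 179 independent participants, not to one that randomises living rooms.

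At 179 complete cases, power was below 80% for every positive ICC examined. The loss is about a percentage point with two per room and ICC .02, and about 25 points with eight per room and ICC .10. Counting all 199 as fully contributing, the range over the clustered rows of the table is 84% down to 60%. These figures rest on assumed room sizes and ICCs, equal room sizes, the stated f(V) = .25 and participant-based degrees of freedom. They are a sensitivity range, not an estimate. The article does not support saying that the trial is underpowered by a known amount, or that 80% is lost under all circumstances.

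**What to change.** Keep n = 199 and rewrite the Power calculation paragraph so that it:

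- says that 179 and 199 assume independent participants;
- gives the expected number of participants per living room and an ICC range for change over time, for example .01 to .10;
- gives the design effect 1 + (m − 1) × ICC and the resulting power, for both 179 complete cases and 199 contributing, or else the detectable f(V) (about .27 at a design effect of 1.2 with 179 analysed);
- as a minor correction, replaces β = .80 with power (1 − β) = .80, described as the target before clustering.

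The cost is one paragraph and a stated power less favourable than 80% over part of the range. It needs no extra participants and no change to conduct or to the planned mixed models.

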### Procedure

For an overview of the study protocol, see Figure 1.

**Figure 1 Fig1:**
[figure not shown]
**Overview of the study protocol.**

#### Inclusion of participants

The selection of residents is based on the criteria mentioned under the heading ‘Participants’, which are verified by means of the medical files of the residents, in consultation with the medical or nursing staff. The selected residents are asked whether they would like to participate, and their legal representative/contact person is contacted to ask for his/her permission as well. Subsequently, the MMSE is administered; if the score is ≤25, and if the person’s vision and hearing is sufficient based on observations during this test, written consent is asked from the legal representative/contact person and from the resident. When at least two residents in a living room agree to participate, the living room can be included in the study by the researcher.

